### Study population

Participants in post-acute phases of recovery after hip fracture (ICD-10 code: S72.0) [58].

#### Inclusion criteria

Older adults (age ≥ 60 years) after hip fracture, who will be discharged from the rehabilitation or orthopedics units of Herzog and Hadassah Hospitals, Jerusalem, between January 2017 and December 2019. Discharge will be from rehabilitation to a non-institutionalized setting. Patients with broadband or Wi-Fi in their home and able to operate an iPad or computer independently. Functional Independence Measure [49] score at rehabilitation discharge: FIM > 90. Every participant will designate a caregiver (a close friend, family member, or support worker) aged over 18, who will agree to cooperate in the research and be present during the interventional phases to promote participants’ retention.

#### Exclusion criteria

Aphasia, cognitive impairment (Montreal Cognitive Assessment scores: MOCA< 21) [59], other degenerative neurological diagnoses, current major depressive or psychotic disorder, or other acute or chronic health condition that will influence their ability to participate in the study.

### Intervention

The aim of the intervention is to improve functional outcomes during the transition from rehabilitation units to community living and facilitate involvement in life roles in the community. The intervention program will be based on the Cognitive Orientation to daily Occupational Performance (CO-OP) [60]. CO-OP reflects a paradigm shift from component-focused rehabilitation traditionally used, to a broader, client centered, occupation based approach. CO-OP has the potential to support the long-term maintenance of therapeutic achievements following a rehabilitation and encourage the generalization and transfer of skills that will likely lead to continued improvement, rather than additional deterioration [61]. The strategy of CO–OP is to focus treatments directly on improving performance in everyday life activity, rather than treating the underlying impairments and hoping for secondary improvement in meaningful activities [62]. The consensus of the literature examining the CO-OP approach suggests that its use in many novel populations and settings is promising and is expanding [63].

CO-OP is a top-down, task-oriented, client-centered approach that uses an iterative process of dynamic performance analysis and guided discovery to enable individuals to identify strategies that will improve performance [63]. Studies that implement these principal elements in their intervention program described supportive results among elderly after hip fracture [30, 33, 64, 65]. The findings indicate that participating in treatment which focuses on individually chosen and personally meaningful activities improves quality of life [33], balance confidence, independence and physical activity [64] with long-term effect [30] and decreased length of hospital stays [65]. Additionally, previous research demonstrated the effectiveness of CO-OP on function-related goals in post-stroke elderly patients [61, 62, 66–68], which suggests that CO–OP may have a broader positive effect on recovery than conventional occupational therapy care [61, 62]. The older adult populations were comprised of those with no diagnosis of dementia, depression, or cognitive impairment upon testing [62, 63].

In line with previous protocol that included post-stroke elderly patients with a parallel cognitive profile [62], participants will be receiving 10 h of training (1-h sessions/week) from a trained occupational therapist. Through dialogues, the therapist directs the individual to discuss the task’s purpose (goal), identify strategies to achieve it (plan), execute these strategies (do), and evaluate their progress and outcome (check). The intervention will be performed by real-time video-conferencing using an iPad® and Skype™, a software program that allows video calls over the Internet. The CO-OP approach administered in a telerehabilitation format was found to be feasible for adults with traumatic brain injury [69].

#### Treatment fidelity

The occupational therapists will record digital audio or take notes each session. The data of the process and content of the intervention will be used to ensure the treatment fidelity of the intervention. Recordings of the first five sessions of the first 5 participants will be monitored. The occupational therapists providing the intervention and an additional research assistant will review the session recordings to ensure that the CO-OP is delivered as intended, following the essential aspects of intervention.

### Control group

The purpose of the control group is to control for changes that may occur with the passage of time in the estimate of the efficacy of the intervention [70]. This group will receive the usual care and rehabilitation by the common routine for patients with hip fracture, and will be discharged with no further therapy as part of the study. In addition, the clinicians will receive no direction from the research study staff.

### Measurements

#### Sample characterization

##### Demographic questionnaire

This will be used to describe self-reported medical and personal details like age, length of hospitalization, weight bearing status and medical services received post discharge.

### Outcome measures

#### Functional Independence Measure (FIM) [71]

The aim of the FIM is to monitor the recovery of functional ability by people undergoing rehabilitation. The FIM is comprised of 18 parameters, each rated on a scale of 1–7 (range = 18–126) according to the degree of assistance required to perform a specific activity.

#### 12-item MOS Short-Form Health Status Survey [72], Hebrew version [73]

This generic HR-QoL instrument focuses on functional status. The questionnaire includes 12 items taken directly from the SF-36 [74] which are used to calculate the Physical and Mental Component Summary. The first question measured by the SF-12 is an acceptable self-rated measure for general health [75].

#### The Geriatric Depression Scale (GDS)-Short [76], Hebrew version [77]

The scale consists of 15 items; each item has two possible answers (yes or no). The highest possible score is 15, which indicates the most severe depressive state.

*The Canadian Occupational Performance Measure (COPM)* [65] will be used for measuring performance and satisfaction with personally identified participation goals. Participants are asked to identify goals and then rate their performance and satisfaction with current status on a scale from 1 to 10, where 10 indicates optimal performance or satisfaction.

#### The Zarit Caregiver Burden Interview (ZBI) [78]

The ZBI includes 22 statements recorded in a 0–4 Likert scale (total score range 0 to 88, where higher scores mean higher burden), which rates the subjective component of burden.

#### Qualitative interview

Semi-structured interviews will be conducted post intervention with the patients in the research groups (*n* = 60) and their caregivers.

(n = 60) to identify barriers and facilitators regarding the telerehabilitation and face-to-face programs.

### Data analysis

Quantitative data will be analyzed using SPSS 21.0. Descriptive statistics will be obtained on the demographic, social and clinical pretest characteristics of subjects in the three groups. Differences in these variables between the intervention and control groups will be examined using either chi-square tests or analysis of variance. Feasibility in the research groups will be calculated according to the of participants who complete the trial.

Repeated-measures MANOVA will be used to test the effects of the group assignments (intervention vs. control), the effects of time (baseline, post-intervention, and 6-month follow-up), and the group-by-time interaction for measuring all the outcomes. Repeated-measures MANOVA is recommended as being straightforward, powerful, and appropriate to treatment outcome investigations [79]. In addition to providing a multivariate analysis of the effect of treatment on the combined changes in all measures and healthcare costs, this approach also provides a univariate analysis of the effect of treatment on each measure, thus allowing an investigation of which measures were most affected by treatment [79]. *p*-Values less than 0.05 are considered to be statistically significant in all comparisons.

All qualitative interviews (patients and caregivers) will be video/audio-recorded and transcribed. Conventional content analysis with constant comparative methods will be used for coding and analysis. All data will be collected anonymously, and access will be restricted to the investigators.

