## Abstract

**Background:**

Most surviving hip-fracture patients experience reduced mobility and lose some of their functional ability, which increases the risk of complications and rehospitalization. Post-discharge transitional programs to reduce readmissions and disabilities have shown some success. Telerehabilitation refers to the use of technologies to provide rehabilitation services to people in their homes. Considering the need for long-term follow-up care for people with hip fracture, in-home telerehabilitation could increase independence, decrease hospital stays and reduce the burden for caregivers. The objective of this study is to investigate the effectiveness of an intervention program based on telerehabilitation on activities of daily living (ADL), quality of life (QOL), depression and burden on caregivers compared to face-to-face home visits and usual care of community-dwelling older adults after hip fracture.

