**Methods/design:**

This will be a three-armed randomized control trial (RCT) including pre/post intervention and follow-up. The trial will include 90 older people with hip fractures who will be randomly assigned to a telerehabilitation group (*N* = 30), face-to-face visits (N = 30) and a control group. The aim of the intervention is to improve the transition from rehabilitation units to community dwelling. It will include 10 videoconferencing/ face-to-face sessions from an occupational therapist in the presence of the primary caregiver. Each session will be utilized to guide the participants to achieve their self-identified goals, focusing on problem-solving for daily life situations and on the ability to implement the discussed strategies for a variety of activities. Outcome measures include Functional Independence Measure (FIM) for evaluation of ADL, SF-12 for evaluation of Health-related QOL, The Geriatric Depression Scale (GDS) and The Zarit Caregiver Burden Scale. Data will be analyzed using Repeated measures MANOVA.

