## Methods

### Study aims

The primary aim of this study is to compare the effectiveness of in-home telerehabilitation and face-to-face home visit intervention programs, as opposed to the standard care currently offered to community-dwelling older adults after hip fracture. The secondary aims of this study are: (1) to evaluate the maintenance of the interventions’ accomplishments 3 months after completion; (2) to estimate the cost-effectiveness of the intervention programs; and (3) to understand the user experience of the patients and caregivers.

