### Trial design, randomization and recruitment

This study is a three-armed, evaluator-blind, randomized control trial (RCT) and will be implemented according to CONSORT guidelines [57]. Participants will be assigned to research and control groups by using a blocked randomized controlled design, stratified based on age. The randomization sequence will be computer generated and will be known only to the responsible investigator.

All participants will be recruited at the time of discharge from hospital. Health professionals employed at the hospital will screen and refer to a research assistant the interested clients who meet the inclusion criteria. The research assistant will obtain informed consent from caregivers and patients prior to randomization and trial inclusion. Participants (*n* = 90) will be randomized after baseline assessment in the three-arm study. The rehabilitation program will be identical in both intervention groups; only the delivery mode will differ: in-home telerehabilitation or face-to-face home visit. The patients allocated to all groups will continue to receive the standard usual care to improve adherence to intervention protocols. All outcomes will be measured at all three time points: Baseline-pretest (T0), immediately following intervention (post intervention 10 weeks) (T1), and a 6-month follow-up (T2) (See Fig. 1).

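### The group effect is stated as intervention versus control, which, pooled or as a three-level omnibus test, does not show how telerehabilitation compares with face-to-face visits and usual care

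*Protocol article*

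**What the plan says.** All references are to the protocol article.

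- **Design.** Trial design, randomization and recruitment: "This study is a three-armed, evaluator-blind, randomized control trial (RCT"). The abstract gives the arms as "telerehabilitation group (*N* = 30), face-to-face visits (N = 30) and a control group"; with 90 participants in total, the control arm is also 30. For the two active arms, "only the delivery mode will differ: in-home telerehabilitation or face-to-face home visit".
- **Objective.** The abstract's Background asks for the effect of telerehabilitation "compared to face-to-face home visits and usual care of community-dwelling older adults after hip fracture". Study aims words the primary aim as "to compare the effectiveness of in-home telerehabilitation and face-to-face home visit intervention programs, as opposed to the standard care" currently offered.
- **Analysis.** Data analysis uses repeated-measures MANOVA to "test the effects of the group assignments (intervention vs. control"), "the effects of time (baseline, post-intervention, and 6-month follow-up"), and the group-by-time interaction. The same section describes "clinical pretest characteristics of subjects in the three groups" and sets p < 0.05 for all comparisons.
- **Sizing.** Sample size calculation uses a two-group comparison of face-to-face home rehabilitation with conventional care: d = 0.8, 5% one-sided, 80% power, 25 per group, 30 after 20% drop-out.

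**The concern.** The sentence that defines the model lists all three levels of time but only two of group. The objective, however, has telerehabilitation facing two comparators, and the two active arms were built to differ in delivery mode alone. A factor with levels intervention and control removes exactly the distinction that the third arm provides.

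A pooled contrast estimates the average of the two active effects. An average of d = 0.4 is the same whether the effects of telerehabilitation and face-to-face are 0 and 0.8, 0.4 and 0.4, or 0.8 and 0. A significant result produced by face-to-face visits could then be reported as support for telerehabilitation. Conversely, if only one mode works, its effect is halved in the average and may be missed.

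**Working it through.** **Inputs**
- From the document: 30 per arm, 20% drop-out, so 30 × 0.8 = 24 completers per arm; d = 0.8.
- Assumed: the effect in each active arm (the document gives none for telerehabilitation), within-arm SD = 1, one outcome at one time point, two-sided 5%.

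**The plan's own figure.** By the normal approximation, n per group = 2(z₁₋α + z₀.₈)² / d².
- Two-sided 5%: 2(1.960 + 0.842)² / 0.64 = 24.5, so 25. This matches the stated 25.
- One-sided 5%: 2(1.645 + 0.842)² / 0.64 = 19.3, so 20. This does not match.

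The stated 25 is thus the two-sided number, so two-sided tests are used below. The one-sided label is a separate matter.

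**Pooled contrast, 48 versus 24.** Noncentrality = d × √(48 × 24 / 72) = 4d, with 70 df. The effect d is the mean of the two active effects. **Pairwise contrast, 24 versus 24.** Noncentrality = d × √(24 × 24 / 48) = 3.46d, with 46 df.

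| Assumed d, telerehabilitation | Assumed d, face-to-face | Pooled d | Pooled power | Telerehabilitation vs usual care | Face-to-face vs usual care |
|---|---|---|---|---|---|
| 0 | 0.8 | 0.4 | 35% | 5% (false positive) | 77% |
| 0.2 | 0.8 | 0.5 | 51% | 10% | 77% |
| 0.4 | 0.8 | 0.6 | 66% | 27% | 77% |
| 0.8 | 0.8 | 0.8 | 88% | 77% | 77% |

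In the first row the pooled test is positive about a third of the time although telerehabilitation does nothing. With a one-sided 5% test the pooled figures in the first and last rows become 48% and 94%, and the pairwise figure becomes 86%.

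**Three-level omnibus test.** Noncentrality λ = 24 × Σ(mean of arm − grand mean)², with F on 2 and 69 df.
- Both active arms at 0.8: 24 × (2 × 0.267² + 0.533²) = 10.24, power 81%.
- Only one at 0.8: the squared deviations have the same sum, so λ = 10.24, power 81%.

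The omnibus test is equally likely to be significant in both cases, so by itself it cannot separate them.

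**Precision of telerehabilitation minus face-to-face.** Half-width of the 95% CI = t(0.975, 46) × √(2/24) = 2.013 × 0.289 = 0.58 SD.

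**Error control.** With two contrasts at 0.025 two-sided each, the power of a pairwise contrast at d = 0.8 and 24 per arm is about 68%.

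**The case against.** A reader might infer that the plan has decided to merge the active arms. The document does not support that. It never says that the arms are combined. It speaks of group assignments in a trial that assigns three groups, refers to three groups in the baseline description, and elsewhere uses loose labels such as research and control groups. The sample size is also set per group from a two-group comparison. A three-level factor described in shorthand is a fair reading. On that reading, part of the point is about follow-up contrasts, which a fuller protocol or analysis plan could hold. What stands is that the article does state a group effect, and neither reading of it answers the abstract's objective.

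A second tempting inference is that the primary aim itself demands telerehabilitation versus face-to-face. Read alone, Study aims sets both programs against standard care and sits comfortably with intervention versus control. The conflict rests mainly on the objective in the abstract.

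A third is that pooling always costs power. It does not: if both arms have d = 0.8, pooling gives 88% against 77%. Nothing in the document suggests that telerehabilitation has no effect, and the content of the two programs is identical, so the 35% figure is one end of a range. None of these figures is the power of the planned repeated-measures MANOVA.

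**Conclusion.** The point holds as a conflict of wording with a real consequence. Followed literally, the stated group effect pools the active arms and cannot show how telerehabilitation compares with face-to-face visits or, on its own, with usual care. Followed as a bare three-level test, it leaves open which arm differs. That the arms will in fact be pooled is plausible but not established.

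With 24 completers per arm and a two-sided 5% test, pooled power runs from 35% (only one active arm at d = 0.8) to 88% (both), against 77% for a pairwise contrast. The attribution problem does not depend on these assumed effects: an average of two effects does not identify either one. The wording should be settled before outcomes are analysed by arm.

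**What to change.** - State group as a three-level factor: telerehabilitation, face-to-face, usual care.
- Pre-specify telerehabilitation versus usual care and face-to-face versus usual care as the contrasts, with stated error control, for example Holm or a fixed testing order.
- Report telerehabilitation minus face-to-face as an estimate with its 95% CI, and state that a non-significant difference will not be read as equivalence. At about ±0.58 SD the interval will usually be too wide for such a claim.
- Keep any pooled intervention-versus-control test as supportive only.

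**Cost.** No change in conduct or data collection, but some loss of power. Each contrast uses about 48 completers instead of 72. If alpha is split to 0.025, power at d = 0.8 is about 68%, below the planned 80%. Holm recovers some of this when the first contrast succeeds. A fixed order keeps 77% for the first contrast but makes the second depend on it. The sponsor should choose between these knowingly.

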### Sample size calculation

The sample size was based on RCT that compared the effectiveness of face-to-face home rehabilitation to conventional care after hip fracture of geriatric patients [64]. The home rehabilitation group showed a higher degree of recovery in self-care using the FIM, (calculated effect size: d = 0.8). The minimum sample size at the significance level of 5% (one-sided test) and power of 80% is 25 in each group. Estimated drop-out rate is 20%; therefore, a maximum of 30 participants will be recruited for each group.

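### None of the named tests isolates the group difference at follow-up, so a significant result does not answer the maintenance aim (secondary aim 1)

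*Protocol article*

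**What the plan says.** Under Study aims, secondary aim 1 is "to evaluate the maintenance of the interventions’ accomplishments 3 months after completion". Under Trial design, randomization and recruitment, "All outcomes will be measured at all three time points: Baseline-pretest (T0), immediately following intervention (post intervention 10 weeks) (T1), and a 6-month follow-up (T2").

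The Data analysis section gives one inferential method for the quantitative outcomes. It begins "Repeated-measures MANOVA will be used to test the effects of the group assignments (intervention vs. control") and continues with "the effects of time (baseline, post-intervention, and 6-month follow-up), and the group-by-time interaction for measuring all the outcomes". A univariate step follows for each measure, "thus allowing an investigation of which measures were most affected by treatment"; it divides the result by outcome, not by visit. The significance rule is general: "Values less than 0.05 are considered to be statistically significant in all comparisons". No test is tied to a particular aim, and there is no criterion for calling a gain maintained.

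**The concern.** Maintenance is a question about T2: does a difference from control remain, and how much of the T1 gain is still there? The named tests answer other questions.

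- **Group-by-time interaction.** Its null is that the arms have parallel profiles over T0, T1 and T2. A benefit at T1 alone breaks that null.
- **Time main effect.** It pools the arms, so it mixes natural recovery with treatment.
- **Group main effect.** It compares the arms on the average of all three visits, including the pre-randomisation baseline.

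If a significant interaction or group effect were reported as evidence of lasting benefit, that claim could rest on the T1 effect alone. The Discussion expects the programme to preserve what rehabilitation achieved, so such a reading would matter.

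**Working it through.** **Inputs.** From Sample size calculation: "calculated effect size: d = 0.8", 25 per group needed, 20% dropout, 30 recruited per group (30 × 0.8 = 24 completers). From Data analysis: significance at 0.05, taken as two-sided. Assumed, because the document gives none: the SDs and correlations between visits. One outcome is considered at a time.

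**The plan's own figure.** n = 2(z₁ + z₂)²/d². Two-sided 5%: 2(1.960 + 0.842)²/0.64 = 24.5, so 25. One-sided 5%, as the text labels it: 2(1.645 + 0.842)²/0.64 = 19.3, so 20. The 25 therefore reproduces as a two-sided figure. That label is a separate matter; 25 per arm is used below.

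**Interaction, algebra.** Write the group difference at (T0, T1, T2), with SD 1.

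- Fully kept: (0, d, d). Mean 2d/3; centred (−2d/3, d/3, d/3); sum of squares (4 + 1 + 1)d²/9 = (2/3)d².
- Fully lost: (0, d, 0). Mean d/3; centred (−d/3, 2d/3, −d/3); sum of squares (1 + 4 + 1)d²/9 = (2/3)d².
- Half kept: (0, d, d/2). Centred (−d/2, d/2, 0); sum of squares d²/2.

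In the kept case T0 stands apart from the other two visits; in the lost case T1 does. The interaction does not register which.

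With equal correlation ρ and n per arm, the noncentrality for two arms is λ = (n/2) × SS/(1 − ρ). For kept and for lost alike, λ = 12.5 × (2/3) × 0.64/(1 − ρ) = 5.33/(1 − ρ). Power comes from the noncentral F on 2 and 47 df.

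| ρ | λ, kept and lost | Rejects: kept | Rejects: lost | Rejects: half kept |
|---|---|---|---|---|
| 0.3 | 7.62 | 66.5% | 66.5% | 53.4% |
| 0.5 | 10.67 | 81.5% | 81.5% | 68.8% |
| 0.7 | 17.78 | 96.4% | 96.4% | 89.6% |

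A three-arm simulation with 24 per arm (2,000 trials per case) agrees within simulation error: kept 67%, 82%, 97%; lost 67%, 84%, 98%. With no effect at any visit it rejects about 5%.

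**Interaction, other structures (two arms of 25).**

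| Structure | Kept | Lost |
|---|---|---|
| AR(1), ρ = 0.5 | 71.8% | 88.3% |
| AR(1), ρ = 0.7 | 90.3% | 99.1% |
| T1–T2 correlation 0.4, others 0.6 | 94.4% | 81.5% |
| Equal ρ = 0.5, T0 SD 0.7 | 92.6% | 85.2% |
| Equal ρ = 0.5, T2 SD 1.3 | 77.8% | 77.8% |

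**Group main effect.** The average difference over visits is 2d/3 = 0.533 if kept and d/3 = 0.267 if lost; the variance of a person's three-visit mean is (1 + 2ρ)/3. Power at ρ = 0.3, 0.5, 0.7: kept 71.6%, 61.9%, 54.2%; lost 24.4%, 20.5%, 17.8%.

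**Tests aimed at T2.** A simple contrast on T2 − T0 change (two arms of 25) rejects 64.9%, 79.1%, 94.7% if kept and 5.0% if lost. The baseline-adjusted comparison at T2 (24 per arm, simulated) rejects 80.4%, 86.8%, 96.0% if kept and 5.6%, 5.6%, 5.0% if lost. The T2 − T1 contrast is the mirror image: at ρ = 0.5, 5.0% if kept and 79.1% if lost.

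**The case against.** The strongest reply is that this is a condensed article. Visit-specific contrasts after a repeated-measures interaction are ordinary follow-up detail, and an analysis plan that is not shown may contain them. Nor does the text say that the interaction will decide secondary aim 1. Both statements are fair, so the absence of a named T2 contrast is not the point here. What stands is that the article does name its tests, for all outcomes over these visits, and those tests do not match an aim it also states. Plotted means would show direction, but no named p-value addresses T2.

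Four stronger readings are tempting, and the document does not support them:

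- *The interaction is the only between-group test that reaches follow-up.* It is not. The group main effect, in the same sentence, also uses T2 and does respond to loss of the gain, though in diluted form.
- *Rejecting 67–98% of the time when the gain is lost is an inflated Type I error.* It is not. With a T1 effect the parallel-profiles null is false and rejection is correct; with no effect at any visit the test keeps to about 5%.
- *The protocol's null is that no benefit remains at T2.* It states none. Maintenance could also mean stability from T1 to T2, which is why the remedy reports both quantities.
- *The interaction always rejects equally often for kept and lost gains.* Equality depends on the covariance structure. It can favour either case.

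**Conclusion.** The point holds as a mismatch between the stated tests and secondary aim 1. Under equal SDs and equal correlations, with d = 0.8 and about 24–25 completers per arm, the interaction cannot tell a fully kept gain from a fully lost one: about 67%, 82% and 97% rejection in both cases at correlations of 0.3, 0.5 and 0.7. In the structures tried where the two rates differ, a fully lost gain was still rejected in 81.5% to 99.1% of trials. The group main effect rejects about 18–24% of the time when nothing remains at T2. A significant result on either test therefore does not show maintained benefit.

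The percentages depend on assumed correlations and a single outcome. The reasoning behind them does not: any T1 effect breaks the interaction null, and in the multivariate version a T1 effect on any one measure is enough. Whether the investigators would in fact read the interaction as evidence of maintenance is not stated. The finding concerns a secondary aim and says nothing against the interaction's role for the primary aim.

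**What to change.** In Data analysis, for secondary aim 1 only:

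1. Compare each active arm with control at T2, adjusted for the T0 value of the outcome, and give the difference with a 95% CI. This shows whether a benefit remains.
2. Beside it, report the arm difference in T1-to-T2 change with a 95% CI. This shows how much of the gain was kept. Read it through its interval, since a non-significant change is not proof of maintenance.
3. State that the omnibus interaction will not be used as evidence of maintenance.

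A plain contrast on T2 − T0 change would also separate the cases; baseline adjustment is preferred because it rejects more often when the gain is kept.

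The cost is one or two sentences and a few additional named contrasts. No extra visits, patients or data are needed.

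### Treating baseline as a level of time dilutes the group main effect to two thirds and leaves group-by-time usually less efficient than adjusting for the T0 score

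*Protocol article*

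**What the plan says.** The Data analysis section of the protocol article fixes the model and its terms. It states that "Repeated-measures MANOVA will be used to test the effects of the group assignments (intervention vs. control"), followed by "the effects of time (baseline, post-intervention, and 6-month follow-up), and the group-by-time interaction for measuring all the outcomes". Baseline is therefore a level of the time factor. The section names no covariate, applies one 0.05 threshold to all comparisons, and does not say which of the three terms carries the treatment claim.

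The section on trial design, randomization and recruitment says "All outcomes will be measured at all three time points: Baseline-pretest (T0), immediately following intervention", with a 6-month follow-up as the third visit (T2). It also says that participants "will be randomized after baseline assessment in the three-arm study". Each outcome's T0 value is therefore a pre-randomisation measurement that is already collected.

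The Sample size calculation gives "calculated effect size: d = 0.8", without saying whether the standard deviation is that of a follow-up score or of a change. No baseline-to-follow-up correlation or standard deviation appears anywhere in the article.

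**The concern.** Two of the listed terms bear on treatment, and both use T0 poorly.

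- **Group main effect.** It is a mean over three visits, one of which precedes randomisation and has no expected difference between arms. It does not estimate the effect after treatment.
- **Group-by-time interaction.** It rests on differences between visits, so T0 enters with a slope fixed at 1 instead of a slope estimated from the data. In a randomised trial this usually costs precision.

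The article plans 30 per arm with 20% drop-out, which leaves 30 × 0.8 = 24 per arm, so precision is scarce. A reader of the results could also take a non-significant group term, diluted by construction, as evidence of no effect. The point holds with complete data and does not depend on how missing visits are handled.

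**Working it through.** **Inputs.** From the Sample size calculation: d = 0.8, 5% level, 80% power, 25 per group, 20% drop-out, 30 recruited per group. Assumed, because the article does not give them: the between-visit correlation rho (range 0.3 to 0.8), equal variances (SD 1) and the same rho between all visits.

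**The plan's own figure.** n per group = 2(z_alpha + z_beta)²/d².
- One-sided 5%: 2(1.645 + 0.842)²/0.64 = 19.3, so 20.
- Two-sided 5%: 2(1.960 + 0.842)²/0.64 = 24.5, so 25.

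The stated 25 matches a two-sided test although the text calls it one-sided. MANOVA F tests are non-directional too, so two-sided is the main case below. The label is a separate matter.

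**Group main effect.** With effect δ at T1 and T2 and none at T0, the estimated effect is (0 + δ + δ)/3 = 2δ/3, whatever rho is. The variance of a three-visit mean is (1 + 2rho)/3. At rho 0.5 this is 0.667, so the effective d is 0.533/√0.667 = 0.653. Power with 24 per arm, two-sided 5%, d on the T1-score scale (noncentral t):

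| rho | Main effect over T0, T1, T2 | Mean of T1 and T2, adjusted for T0 |
|---|---|---|
| 0.3 | 69.7% | 95.2% |
| 0.5 | 60.1% | 97.0% |
| 0.7 | 52.5% | 99.5% |

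**Single change contrast against baseline adjustment.** The change-score variance is 2(1 − rho); with T0 as covariate it is 1 − rho². The ratio is (1 + rho)/2, below 1 for every rho below 1. If d is on the change scale, the adjusted effective d is 0.8/√((1 + rho)/2); at rho 0.5 this is 0.8/√0.75 = 0.924. If d is on the T1-score scale, the effective d is 0.8/√(2(1 − rho)) for change and 0.8/√(1 − rho²) adjusted. Two arms, 24 per arm, two-sided 5%:

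| rho | d on change scale: change → adjusted | Gain (points) | Gain if d on T1-score scale (points) |
|---|---|---|---|
| 0.3 | 77.4% → 92.0% | 14.6 | 18.1 |
| 0.5 | 77.4% → 88.0% | 10.5 | 10.5 |
| 0.7 | 77.4% → 83.7% | 6.3 | 2.9 |
| 0.8 | 77.4% → 81.6% | 4.2 | 0.5 |

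With a one-sided test at rho 0.5 the gain is about 7 points.

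**Omnibus interaction, three arms and three visits.** Simulated with 4,000 runs, 24 per arm, both active arms at d = 0.8 on the T1-score scale. With a sustained effect, interaction against baseline-adjusted joint test: 66% against 92% at rho 0.3, 82% against 95% at 0.5, 97.6% against 99.3% at 0.7. With an effect at T1 only, the gaps are about 8.5, 4.5 and 0.4 points.

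**Unequal variances.** Let b be the regression slope of T1 on T0, V the T0 variance and R the residual variance. The change variance is R + (1 − b)²V; the adjusted variance is R. With b = 0.5 and V = 1, R = 0.75 and the change variance is 0.75 + 0.25 = 1.00, which gives the 10.5-point gain (d = 0.8 on the change scale). Halving V with b and R unchanged gives 0.75 + 0.125 = 0.875, and the gain falls to 6.0 points.

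**The case against.** The strongest reply is that the interaction is a valid test. With three arms and three visits it tests the T1 − T0 and T2 − T0 changes jointly, and under randomisation it is unbiased. The Data analysis section speaks of the treatment effect in terms of combined changes in the measures, which suggests that the interaction, not the group main effect, is meant to carry the claim. All of that stands. It limits the point to efficiency and to a listed main effect that should not be read as the treatment effect. It does not remove either, because the section never names the deciding test and counts p below 0.05 as significant for every comparison.

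Three stronger readings are tempting and are not supported.

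- A reader might infer a fixed loss of about 10 power points. That figure needs rho near 0.5, equal variances and one two-sided, two-arm contrast. The article gives no rho.
- A reader might infer that the entry rule "Functional Independence Measure [49] score at rehabilitation discharge: FIM > 90", on a scale ending at 126, lowers rho and so enlarges the loss. The formula (1 + rho)/2 assumes equal variances, and restricting the baseline range breaks that assumption. Under selection on baseline with a linear relation, the loss shrinks, as the last step of the working shows.
- A reader might infer that the interaction ignores T0. It uses T0, but with the slope fixed at 1.

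A fair practical objection also stands: the article plans a joint multivariate test over all measures and healthcare costs, and outcome-by-outcome models would replace it or make it supportive.

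**Conclusion.** The point holds as an efficiency defect plus a diluted term, not as a validity error.

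The two-thirds dilution of the group main effect needs only an equal effect at T1 and T2 and no expected difference at T0. Its power of about 60% also assumes d = 0.8, 24 per arm, a two-sided 5% test and rho 0.5.

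The gain from baseline adjustment over a single change contrast is a range: about 15 to 4 points over rho 0.3 to 0.8 if d is on the change scale, and 18 to under 1 point if it is on the T1-score scale. The wording "The home rehabilitation group showed a higher degree of recovery in self-care using the FIM, (calculated effect size: d = 0.8") does not settle which scale applies. The gain is smaller for a one-sided test, a restricted baseline variance, or an omnibus test with an effect at T1 only. At high rho little is lost on the interaction, but that is where the main effect is weakest (52.5% at rho 0.7). Adjustment is worth making because the T0 data are already collected.

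**What to change.** In the Data analysis section:

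1. For each outcome with a T0 value, model T1 and T2 as responses with that outcome's own T0 value as covariate, and test the arm contrasts at T1 and at T2. A longitudinal model that keeps T0 as a response but constrains the baseline means to be equal across arms serves the same purpose.
2. Name these contrasts as the treatment test.
3. State that the group main effect averaged over T0 is not interpreted as the treatment effect.
4. If the joint multivariate test is kept, run it on T1 and T2 with the T0 values as covariates, or label it supportive. Healthcare costs need no T0 covariate if none is collected.

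The cost is a change of wording, about one degree of freedom per outcome model, and a joint MANOVA that is respecified or becomes supportive. No new data or participants are needed.
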